#### Treatment modality

To explore if there are differences in (cost-)effectiveness between both treatment modalities (i.e., group format and individual format), we will perform some additional analyses. Specially, we will compare TAY who received ACT your way in a group with TAY who received ACT your way individually. Moreover, to rule out treatment modality effects, we will compare TAY who received ACT your way in a group with TAY who received TAU in a group and TAY who received ACT your way individually with TAY who received TAU individually.

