### Study design and procedure

The study is designed as a multi-center, randomized controlled trial (RCT). Data will be collected in 14 Dutch and Belgian mental healthcare institutions. Within each institution, TAY meeting the inclusion/exclusion criteria, their parents/caregivers and their therapists will be asked to participate in the study. Parents/caregivers of adolescents younger than 16 will be directly involved in the study. TAY aged 16 and older will be asked first for permission to contact their parents/caregivers. If they agree, their parents/caregivers will be asked to participate in the study as well. Before enrolling in the study, written informed consent from TAY and parents/caregivers/legal representatives (for adolescents younger than 16) will be obtained. If parents/caregivers and therapists agree to participate, they will be asked for their own written informed consent as well.

In total, six multiple informant (TAY, parents/caregivers, therapist) assessments will be conducted: at baseline (T0), after 3 sessions (T1), after 6 sessions (T2), after 9 sessions (T3), at post-intervention (T4) and at 6-month follow-up (T5). Assessments will include diagnostic interviews (at T0, T4 and T5) and questionnaires (at T0 to T5). The assessments will be conducted by research assistants working at the participating institutions (e.g., master students and psychologists). Research assistants will be trained in administering the diagnostic interview and questionnaires. The TAY will receive a 30 euro gift card as a reward (5 euros per assessment). After the baseline assessment (T0), TAY will be randomly assigned to either the ACT your way or TAU condition using a computer generated block design. At each institution, five participants will be randomly allocated to the ACT your way condition and five participants will be randomly allocated to the TAU condition (blocksize = 10). See Fig. 1 for an overview of the study design.

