### Study conditions

#### ACT your way

ACT your way consists of 12 weekly sessions, that can be carried out both individually as in groups. The therapists at the clinical institutions decide if they carry out ACT your way individually or in a group. There is a guide for therapists [66], a workbook for TAY [67] and a website with additional videos, mindfulness exercises and information for TAY. Each session lasts either 120 (group therapy) or 60 (individual therapy) minutes and has a fixed format in which psychoeducation, mindfulness exercises, metaphors and experiential exercises are carried out. The 12 sessions are divided into four blocks, each comprising of three sessions. The first block focusses on values (i.e., desires regarding development, identity, and autonomy). The second block focusses on the six core processes of psychological inflexibility (i.e., experiential avoidance, cognitive fusion, dominance of conceptualized past and feared future, attached to the conceptualised self, lack of values, and inaction). The third block focuses on acquiring skills based on the six core processes of psychological flexibility (i.e., acceptance, cognitive defusion, contact with the present moment, self as context, values, and committed action). With these skills, TAY can consciously choose behaviours that fit their chosen values. The fourth block focusses on continuing and strengthening TAY’s psychological flexibility and preparing the TAY for possible relapses in the future. In this study, ACT your way will be carried out in a face-to-face format by therapists working at the participating mental healthcare institutions. The therapists will be trained in using ACT your way (i.e., a two day training in the basics of ACT and a two day training in ACT your way specifically). Moreover, during the course of the study, the therapists will be supervised by an ACT expert.

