#### Treatment as usual

TAU can also be carried out both individually as in groups and will consist of a broad range of different psychological interventions, such as CBT, parent counselling, emotion regulation training, running therapy, or psychodynamic therapy. Therapists of the participating mental health care institutions decide what intervention(s) are most suitable to be carried out as TAU. We expect that in most cases, similar to ACT your way, TAU will also consist of weekly sessions. However, in the few cases that this is not possible, it is also acceptable to have bi-weekly sessions within TAU. If TAU is carried out bi-weekly, the T1, T2, T3 and T4 will take place after 2, 4, 6 and 8 sessions, respectively. We choose this option as then both in the ACT your way as TAU condition, the assessments will take place approximately around the same time.

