#### Other characteristics

*Treatment integrity* will be established by video/audio recording two randomly chosen ACT your way sessions per client (in the case of individual therapy) or group (in the case of group therapy). The sessions will be rated by an independent researcher with a checklist that has been developed in an earlier study [44]. The checklist is based on ACT literature and input from various ACT experts. The checklist can be used to assess which of the six core processes of ACT (i.e., acceptance, defusion, contact with the present moment, self as context, values and committed action) and ACT techniques (i.e., psychoeducation, mindfulness exercises, metaphors and experiential exercises) are carried out per session and if the goal of the session is obtained.

*The content of TAU* will be measured with a short version of the Therapy Procedure Checklist (TPC) [110] at T1, T2, T3 and T4. For each client, therapists fill out how many sessions took place after the previous assessment moment. Then, for each session, therapists indicate which techniques they used in the session (e.g., CBT or psychoeducation), if the session was individual or in a group and if the session was online or offline (for TAU only).

The Life Event Scale (LES) [111] will be used to gather information about several *life events* at T0, T4 and T5. The LES contains 23 questions about various life events (e.g., drug abuse, bereavement, maltreatment and suicide attempts). For each life event, participants are asked to indicate when the event took place (i.e., “*last week”, “last year”, “more than one year ago”*) and to what extent the event made them upset (i.e., ranging from 0 = “*not*” tot 3 = “*very*”). The LES has been used in previous research [94].

*Costs* will be measured with a cost diary based on the Trimbos Institute and Institute of Medical Technology Assessment Questionnaire on Costs Associated with Psychiatric Illness (TiC-P) [112] and PRODISQ [113]. With the cost diary, we will register direct healthcare costs (e.g., visits to healthcare professionals or alternative care), direct non-healthcare costs (e.g., formal and informal care), indirect costs (e.g., productivity losses caused by absence and reduced productivity and school) and out of pocket costs (e.g., transport or parking costs). The cost diary has been used in previous research (e.g., [114]).

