The presented study design has some potential challenges that could turn into limitations if not handled properly. Hence, for each potential challenge, a solution to overcome this challenge will be discussed. First, in the current study, ACT your way will be carried out both in an individual as in a group format, making it more difficult to isolate intervention effects from treatment modality effects. We decided to carry out ACT your way both individually as in groups, as both treatment modalities have their own potential advantages. For instance, group interventions might provide more opportunities for normalization, positive peer modeling and social support, whereas within individual interventions, therapists can more easily adapt exercises and subjects to the specific wishes and needs of each client. To isolate intervention from treatment modality effects, we will perform additional analyses in which we explore possible differences between both treatment modalities (see Method section). Second, the TAU condition might be heterogeneous in content and duration, which makes it challenging to compare the effects of ACT your way with the effects of TAU. To address this challenge, we will ask all therapists in the TAU condition to write down the content and duration of each session. Subsequently, we will investigate if there are differences in duration between ACT your way and TAU. If there are differences, the duration of treatment will be added as covariate in all analyses. Third, recruiting a sample of 140 TAY in 24 months could be challenging. To reach this sample size, we will cooperate with fourteen mental health care institutions in the Netherlands and Belgium. Moreover, to promote participation, we will give TAY a 30 euro giftcard as a reward and only use online questionnaires that TAY, parents/caregivers and therapists can easily fill out at home. Last, non-response and/or drop-out can also be a potential challenge. To minimize non-response, we built a website, including a system that automatically sends research assistants weekly updates via mail, that helps research assistants to monitor the assessment progress. At the website and in the weekly updates, research assistants can easily see which questionnaires are filled out or not and which ones are planned. With the help of this website and automatic mailing system, researchers can directly react to non-response and increase the response rate of the study. To minimize measurement drop-out, we will motivate TAY to continue participating by sending them thank you emails and newsletters and handing out a 5 euro gift card after each assessment. Moreover, when participants drop out of treatment, we will still ask them to fill out the post-intervention and follow-up assessments. Furthermore, to avoid potential bias due to drop-out, all analyses will be carried out according to the intention to treat principle.

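### The comparisons by format received cannot rule out or isolate treatment modality effects, because format is chosen by clinicians and is neither randomised nor fixed before allocation

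*Protocol article*

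**What the plan says.** All references are to the protocol article.

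- **What is randomised.** Under Study design and procedure: "At each institution, five participants will be randomly allocated to the ACT your way condition and five participants will be randomly allocated to the TAU" arm, in blocks of ten. Format is not mentioned as a stratification factor.
- **Format of ACT your way.** Under ACT your way: "The therapists at the clinical institutions decide if they carry out ACT your way individually or in a group".
- **Format of TAU.** Under Treatment as usual: "TAU can also be carried out both individually as in groups and will consist of a broad range of different psychological interventions". The same section adds: "Therapists of the participating mental health care institutions decide what intervention(s) are most suitable to be carried out as TAU". That sentence concerns the intervention. That therapists thereby also choose the format is an inference.
- **Recording of TAU format.** Under Other characteristics, the TAU checklist records for each session whether it was individual or in a group.
- **Planned comparisons.** Treatment modality first plans, as exploration: "we will compare TAY who received ACT your way in a group with TAY who received ACT your way individually". It then states: "to rule out treatment modality effects, we will compare TAY who received ACT your way in a group with TAY who received TAU", again in group format, with the parallel comparison for the individual format.
- **Claimed result.** The Discussion lists the mix of formats as the first challenge of the design and answers it thus: "To isolate intervention from treatment modality effects, we will perform additional analyses".
- **Adjustment.** Effectiveness adds institution dummies to all analyses and controls for the baseline level of the outcome.

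**The concern.** The article names a confounder, the mix of group and individual delivery, and offers these comparisons as the remedy. To rule out or isolate a modality effect, the compared subsets must differ only in the factor of interest. Here each subset is formed by a clinical decision that is not randomised, may be made after allocation, and may follow a different rule in each arm. A difference between subsets, or the absence of one, could then partly reflect who is placed in groups. If the wording stands, the trial report could draw a causal conclusion about format, or about ACT within a format, that the design does not secure.

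**Working it through.** **Step 1. Set the passages side by side.** Condition is randomised within institution, and format is not. The ACT format is a therapist decision, and the TAU format is probably one too. Sample size calculation says that most therapists deliver only one of the two conditions, so mostly different people decide in each arm. The article states no common rule, no declaration before allocation and no matching of format within an institution. The subsets are defined by format received.

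- *ACT group versus ACT individual*: both subsets lie within one randomised arm, so randomisation plays no part in the comparison.
- *ACT group versus TAU group, and individual versus individual*: randomisation protects these only if the same kind of participant enters a given format in both arms.

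**Step 2. Inputs for size.** The documents give only the planned effect, 0.50 SD (Sample size calculation). Everything else here is assumed: half of each arm in each format, one prognostic factor with correlation ρ with the outcome, and a format choice whose underlying index has correlation r with that factor. The mean of the upper half of a standard normal is 0.798.

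- Matched-format bias, selection in one arm only: ρ × r × 0.798.
- Within-ACT bias, selection in the ACT arm: 2 × ρ × r × 0.798.

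**Step 3. Matched-format bias, selection in one arm only.**

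| ρ | r | Bias (SD) |
|---|---|---|
| 0.3 | 1.0 (perfect) | 0.3 × 1.0 × 0.798 = 0.24 |
| 0.3 | 0.5 | 0.3 × 0.5 × 0.798 = 0.12 |
| 0.3 | 0.3 | 0.3 × 0.3 × 0.798 = 0.07 |

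With selection kept perfect, ρ from 0.1 to 0.5 gives 0.08 to 0.40 SD.

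**Step 4. Dependence on the selection rule.** A large simulation set the true treatment and format effects to zero, used ρ = 0.5, and let format follow a probit on the prognostic factor with slope 0.5, so r = 0.5/√1.25 = 0.447. No institution or baseline adjustment was applied.

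| Selection into group format | Group vs group | Individual vs individual | ACT group vs ACT individual |
|---|---|---|---|
| None in either arm | 0 | 0 | 0 |
| Same rule and same share in both arms | 0 | 0 | 0.36 |
| In the ACT arm only | +0.18 | −0.18 | 0.36 |
| Opposite in the two arms | +0.36 | −0.36 | 0.36 |
| Same slope, group share about 67% vs 33% | −0.13 | −0.13 | 0.37 |

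The third row agrees with the formula: 0.5 × 0.447 × 0.798 = 0.18. The matched contrasts are unbiased when the rule and the share agree between arms. The within-ACT contrast is biased whenever selection into format in the ACT arm depends on prognosis.

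**Step 5. Power of the alternative test.** For a condition-by-format term in all 140 participants, assume four cells of 35 and a design effect of 1 + (2 − 1) × 0.05 = 1.05. The standard error is √(4 × 1.05/35) = √0.12 = 0.346. For an interaction of 0.50 SD, 0.50/0.346 = 1.44, and Φ(1.44 − 1.96) is about 0.30.

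**The case against.** The case for leaving the plan alone has real content.

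- *The analyses are exploratory.* The section opens with that word and calls them additional. This stands, and it limits the importance of the point. It does not cure the two stronger claims, one of which is presented in the Discussion as the solution to a named challenge.
- *Site differences are handled.* Allocation is balanced within institution, and institution dummies and baseline control are planned. A reader might infer that the matched subsets simply come from different sites. The article does not support that, because the dummies, if applied here as stated, absorb much of the between-site difference. What remains is selection within a site that differs between arms. In addition, a site that uses groups in one arm and individual sessions in the other contributes no within-site matched contrast.
- *Bias is not shown.* Correct. If each institution used one format for both arms, fixed beforehand, the matched contrasts would keep randomisation within institution. The article neither says this nor excludes it. A reader might infer that the matched results must reflect selection, but the most that follows is that they may be mixed with it.
- *Half the planned effect is an exaggeration.* Also correct. The 0.24 SD requires perfect selection on one factor in one arm and none in the other, and no input to it comes from the documents.
- *TAU premises.* Therapist choice of TAU format is inferred. Session-level recording shows that mixed TAU is possible, not that it occurs, and it provides data to classify such cases. The classification rule may be left to a fuller document.
- *Small subsets.* The article claims no power for these comparisons and gives no split by format, so their size is not an error.

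**Conclusion.** The point holds as a claim wrongly stated. ACT in groups versus ACT individually is observational. The matched-format contrasts are protected only under a condition that the article does not state: the same rule for choosing format in both arms, or format fixed before allocation. Neither comparison can deliver what *rule out* and *isolate* promise.

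The size of any bias is unknown. Under the assumptions shown, with a factor correlated 0.3 with the outcome and selection in one arm only, the matched contrasts would be off by about 0.07 to 0.12 SD for moderate selection and 0.24 SD in the worst case. These figures ignore any reduction from the institution dummies.

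A reader might go further and infer that the trial's main result is compromised. It is not: the primary ACT versus TAU contrast follows the randomised condition and does not use format. The consequence is confined to conclusions about modality.

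**What to change.** 1. Delete *rule out* in Treatment modality and *isolate* in the Discussion. Describe all three format-received comparisons as exploratory and non-randomised, and draw no causal conclusion about modality from them. This costs only wording and can be done at any stage.
2. Where still feasible, have the site record before randomisation the format intended for each participant under ACT your way and under TAU. Define the subgroups from these entries, and estimate a condition-by-intended-format term in the full randomised sample.

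The second step costs two items on the baseline form, and clinicians at 14 institutions must name an intended TAU format before allocation. Some participants will then receive a format other than the intended one. With power of about 0.30 for a 0.50 SD interaction in equal cells, the result is descriptive only. Recruitment was planned for March 2022 to March 2024, so for participants already randomised only the first step remains.

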## Discussion

The current study protocol describes the design of a multi-center RCT in which we will evaluate the effectiveness and cost-effectiveness of ACT your way compared to TAU. The study will be conducted within a relatively large sample of TAY with diverse psychological disorders. Besides studying the (cost-)effectiveness, we will also investigate for whom and under what circumstances (i.e., moderation analyses) and how (i.e., mediation analyses) ACT your way is (most) effective.

The presented study design has some potential challenges that could turn into limitations if not handled properly. Hence, for each potential challenge, a solution to overcome this challenge will be discussed. First, in the current study, ACT your way will be carried out both in an individual as in a group format, making it more difficult to isolate intervention effects from treatment modality effects. We decided to carry out ACT your way both individually as in groups, as both treatment modalities have their own potential advantages. For instance, group interventions might provide more opportunities for normalization, positive peer modeling and social support, whereas within individual interventions, therapists can more easily adapt exercises and subjects to the specific wishes and needs of each client. To isolate intervention from treatment modality effects, we will perform additional analyses in which we explore possible differences between both treatment modalities (see Method section). Second, the TAU condition might be heterogeneous in content and duration, which makes it challenging to compare the effects of ACT your way with the effects of TAU. To address this challenge, we will ask all therapists in the TAU condition to write down the content and duration of each session. Subsequently, we will investigate if there are differences in duration between ACT your way and TAU. If there are differences, the duration of treatment will be added as covariate in all analyses. Third, recruiting a sample of 140 TAY in 24 months could be challenging. To reach this sample size, we will cooperate with fourteen mental health care institutions in the Netherlands and Belgium. Moreover, to promote participation, we will give TAY a 30 euro giftcard as a reward and only use online questionnaires that TAY, parents/caregivers and therapists can easily fill out at home. Last, non-response and/or drop-out can also be a potential challenge. To minimize non-response, we built a website, including a system that automatically sends research assistants weekly updates via mail, that helps research assistants to monitor the assessment progress. At the website and in the weekly updates, research assistants can easily see which questionnaires are filled out or not and which ones are planned. With the help of this website and automatic mailing system, researchers can directly react to non-response and increase the response rate of the study. To minimize measurement drop-out, we will motivate TAY to continue participating by sending them thank you emails and newsletters and handing out a 5 euro gift card after each assessment. Moreover, when participants drop out of treatment, we will still ask them to fill out the post-intervention and follow-up assessments. Furthermore, to avoid potential bias due to drop-out, all analyses will be carried out according to the intention to treat principle.

Notwithstanding the potential challenges, the study has some important strengths. First, this study will be carried out in a transdiagnostic sample of clinically referred TAY. By recruiting a diverse sample of TAY with various forms of psychopathology (e.g., anxiety disorder, OCD, trauma, depressive disorder, ODD, CD), the results of the study will be generalizable to a large population of clinically referred TAY. Second, the study will be executed within fourteen mental health care institutions in the Netherlands and Belgium. By conducting the study under these real life conditions, the study will have a large ecological validity and will allow us to make conclusions about the real-world (cost-)effectiveness of ACT your way for TAY. Third, in contrast to many earlier studies examining the effects of ACT in youth, we will use a rigorous research design. More specifically, we will conduct an RCT, compare the effects of ACT your way with an active control condition, investigate both short and long term effects of ACT and use a multi-informant (i.e., TAY, parents/caregivers and therapists) and multi-method (i.e.,, questionnaires and diagnostic interviews) approach. When appropriately conducted, RCT’s are seen as the golden standard for intervention research [63] making it is possible to make more grounded conclusions about the (cost-)effectiveness of ACT your way. Moreover, by using an active control condition we are able to say something about the (cost-)effectiveness of ACT compared to routine care. This is more useful than comparing ACT to a waitlist or medication only condition. Furthermore, due to the six month follow-up measure, we can also examine the long term effects of ACT, including possible sleeper effects or recurrence of psychological problems. In addition, using a multi-informant and multi-method approach will decrease the risk for common method bias [117].

Besides the strengths, the study also has some important implications for clinical practice. First, ACT your way is specifically developed for TAY. Developing interventions specifically for TAY and studying the effects of such interventions is clinically important as, compared to other age groups (i.e., younger adolescents and older adults), TAY experience more psychological problems and are less likely to receive age-appropriate treatments. Developing and investigating the effects of interventions for TAY can contribute to improving the continuity of mental health care from adolescence to young adulthood. Second, ACT your way is a transdiagnostic intervention. Examining the effects of transdiagnostic interventions is clinically relevant as they have potential benefits over traditional interventions. Particularly, within transdiagnostic interventions, various psychological symptoms can be treated within one intervention which potentially contributes to the efficiency and (cost-) effectiveness of mental health care. Moreover, transdiagnostic interventions seem specifically relevant for TAY, as comorbid problems, shifting symptom profiles and changing therapy needs are often present during this developmental phase [18, 19]. Third, to our knowledge, this will be the first study investigating the cost-effectiveness of ACT in TAY. Although there are few studies that investigated the cost-effectiveness of ACT in adult samples (e.g., [118]), no cost-effectiveness studies have been conducted in youth. Cost-effectiveness studies are important to inform policy makers about the specific costs and benefits of certain interventions. Last, besides studying the (cost-) effectiveness of ACT, we will also investigate potential moderators and mediators. Studying moderation effects can inform clinical practice for whom and under what circumstances ACT your way is most effective. Moreover, if ACT your way is effective, then it is scientifically and clinically relevant to understand through which mechanisms ACT your way works (mediation analyses). Moreover, by investigating these mechanisms, we can test the theory behind ACT.

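### Adding treatment duration as a covariate in all analyses when the arms differ on it replaces the effect of assignment with another quantity and may bias the results

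*Protocol article*

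**What the plan says.** The rule stands in the Discussion of the protocol article, as the answer to the second potential challenge, that TAU may vary in content and duration. First, "we will ask all therapists in the TAU condition to write down the content and duration of each session". Then: "Subsequently, we will investigate if there are differences in duration between ACT your way and TAU". Then: "If there are differences, the duration of treatment will be added as covariate in all analyses".

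The last challenge in the same section adds that "to avoid potential bias due to drop-out, all analyses will be carried out according to the intention to treat principle".

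The Effectiveness section describes a model with condition, the baseline value of the outcome and institution dummies, fitted separately at T4 and T5. Duration is not in it. The opening of Data analysis adds baseline variables that differ between arms. Nowhere does the article keep an analysis without duration as primary once the rule applies, or label the adjusted one a sensitivity or exploratory analysis.

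On what determines duration:
- Randomisation follows the baseline assessment (Study design and procedure).
- "ACT your way consists of 12 weekly sessions, that can be carried out both individually as in groups", and "Each session lasts either 120 (group therapy) or 60 (individual therapy) minutes and has a fixed format" (ACT your way).
- "Therapists of the participating mental health care institutions decide what intervention(s) are most suitable to be carried out as TAU" (Treatment as usual). TAU sessions may be weekly or, in a few cases, bi-weekly.
- Treatment drop-out is a secondary outcome that ACT your way is expected to reduce (introduction, first aim).

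**The concern.** A baseline covariate cannot be changed by treatment, so adjusting for it leaves the randomised comparison intact. Duration can be changed by treatment. Part of it is the treatment, since one arm has a set course and the other does not share it. Part of it is drop-out, which the trial expects to differ between arms.

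Conditioning on such a variable has two consequences. It removes whatever part of the effect runs through duration. It also makes the arms comparable on duration at the price of making them unequal on anything unmeasured that drives both duration and outcome, such as motivation or severity not captured at baseline. The rule applies only when the arms differ on duration, which is the condition under which either consequence can shift the estimate.

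At stake is the meaning of the primary results. The trial sets out to compare ACT your way with routine care as delivered. A duration-adjusted coefficient asks what the difference would be at equal duration, and it answers that only if no unmeasured common causes exist. Because the rule covers all analyses, it also reaches two outcomes where the covariate is nearly part of what is measured: drop-out, which largely fixes duration, and cost-effectiveness, where length of treatment feeds the costs.

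**Working it through.** **1. The plan's own figure.** From the Sample size calculation: effect 0.50, ICC 0.05, 70 therapists, two TAY each, alpha 0.05 (taken as two-sided), power 0.8. For a two-level cluster design, λ = J·d² / {4·[ICC + (1 − ICC)/n]} = 70 × 0.25 / [4 × (0.05 + 0.95/2)] = 17.5 / 2.1 = 8.33. With 1 and 68 degrees of freedom the power is 0.812. The 140 is reproduced. The duration rule does not affect that figure, but 0.50 is the yardstick for what follows.

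**2. Status of duration.** Randomisation comes first. Duration then follows from the arm's format, the therapist's choice of TAU, and whether the participant stays. It is post-randomisation whether counted in weeks, sessions or minutes.

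**3. Bias when the rule applies.** For a linear model:

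adjusted estimate = total effect − (within-arm slope of outcome on duration) × (mean duration in ACT − mean duration in TAU).

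With duration in within-arm SD units, the size of the shift is r × D × residual SD. Here r is the within-arm correlation of duration with the outcome given baseline, and D is the arm difference in SD. The documents give neither r nor D, nor the baseline–outcome correlation. All three are assumed. With a baseline–outcome correlation of 0.5, residual SD = √(1 − 0.25) = 0.866.

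| r (absolute) | D | Shift (SD) | A true 0.50 becomes |
|---|---|---|---|
| 0 | any | 0 | 0.50 |
| 0.2 | 0.5 | 0.866 × 0.2 × 0.5 = 0.09 | 0.41 or 0.59 |
| 0.3 | 0.5 | 0.866 × 0.3 × 0.5 = 0.13 | 0.37 or 0.63 |
| 0.4 | 1.0 | 0.866 × 0.4 × 1.0 = 0.35 | 0.15 or 0.85 |

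The last column gives both values because neither the sign of r nor which arm is longer is known.

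**4. Check by simulation.** Settings: 140 participants, 5,000 runs per setting, ordinary least squares without the therapist level, outcome SD 1 within arm, TAU assumed longer by 0.5 or 1 SD. Without duration, the mean estimate was 0.498 to 0.503 for a true 0.50, and a true null was rejected in about 5% of runs. With duration added:

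| Assumed link between duration and outcome | True 0.50, D = 0.5 | True 0.50, D = 1 | True 0, D = 1: rejected |
|---|---|---|---|
| None | 0.50 | 0.50 | 5% |
| Longer helps, +0.3 SD per SD | 0.65 | 0.80 | 37% |
| Longer goes with worse outcome, −0.3 | 0.35 | 0.20 | 38% |
| Shared unmeasured cause, either sign | 0.38 or 0.63 | 0.25 or 0.75 | 27% or 28% |
| Opposing direct and shared-cause paths | 0.53 | 0.55 | 6% |

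These agree with the formula: for example 0.50 + 0.3 × 0.5 = 0.65. The opposing-path row has a net slope of 0.3 − 0.25 = 0.05, hence 0.50 + 0.05 × 1 = 0.55.

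**5. Precision when there is no link.** With 1:1 allocation the variance of the arm effect is multiplied by 1 + D²/4, which is 1.06 at D = 0.5 and 1.25 at D = 1. By the normal approximation with a design effect of 1.05 (effective 70/1.05 = 66.7 per arm), power falls from 0.82 to 0.80 and 0.73 respectively.

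**The case against.** The authors' worry is legitimate: a heterogeneous TAU makes the contrast hard to interpret, and a reader may fairly ask whether a difference reflects content or amount of treatment. That question can be explored. It is a different question from the effect of assignment, it needs an assumption of no unmeasured common causes, and it cannot take the place of the randomised comparison in every analysis.

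Several stronger readings are tempting, and the documents do not support them.

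- *That every effect estimate is biased.* The rule is conditional on a difference, and a given outcome is biased only if duration affects it or shares causes with it. At r = 0 there is only a loss of precision, and opposing paths can nearly cancel.
- *That the rule contradicts the intention-to-treat statement.* That statement is made about drop-out bias, and the plan asks those who stop treatment to complete the post-intervention and follow-up assessments. It governs who is analysed and in which arm; a covariate changes neither. What remains is a tension over what is being estimated.
- *That TAU is open-ended, or that non-responders stay longer.* The article says neither. It says only that TAU might vary in duration.

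The assessment schedule also deserves credit. For bi-weekly TAU, T1 to T4 are moved to 2, 4, 6 and 8 sessions so that assessments fall at about the same time, which may narrow the difference in weeks of treatment before T4. It does not do so for sessions: such a participant has had 8 by T4, against a 12-session course in ACT your way. Finally, the simulation ignores therapist clustering and gives both arms the same spread of duration, which need not hold when one arm has a set course.

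**Conclusion.** The concern stands in conditional form. If the arms differ in duration, the plan as written replaces the effect of assignment with a duration-adjusted quantity in all analyses and keeps no unadjusted analysis as primary. The adjusted result may be biased for any outcome linked to duration, in either direction, and is otherwise less precise. For drop-out and cost-effectiveness the adjustment is hard to interpret at all.

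Whether the rule would apply cannot be known from the article. Its own expectations make that plausible: ACT your way is expected to lower drop-out, and the introduction sets 20.6% in the pilot against 41% to 57% in a CBT trial for the same target group.

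The sizes illustrate possible harm and do not forecast it. They run from no bias to roughly 0.35 SD in the table of assumed correlations, the upper end being about 70% of the planned 0.50 (0.35/0.50). They rest on assumed correlations, arm differences and baseline–outcome correlation. The case against the rule rests on duration being post-randomisation and partly defined by the arm, which the article itself establishes.

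**What to change.** Delete the sentence that adds duration as a covariate. The primary analysis of every outcome then remains the model without duration: condition, baseline outcome, institution dummies, and whatever baseline covariates the plan otherwise specifies. The separate rule on baseline differences in Data analysis is not touched by this point.

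Report weeks of treatment and number of sessions by arm descriptively. If the question of amount of treatment matters, present a duration-adjusted or dose analysis as a labelled exploratory analysis, with its assumption of no unmeasured common causes stated, and leave drop-out and cost-effectiveness out of it.

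The cost is a sentence or two of plan text. The sample size, sites and assessment schedule do not change. Describing duration in both arms needs session counts for ACT your way participants as well as for TAU.
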